### 4.2 Inclusion criteria

- admission into the Roessingh Rehabilitation Centre
- unilateral ischaemic or haemorrhagic hemiparetic stroke (single and first ever or history of previous stroke with full physical recovery)
- time since stroke max 6 weeks
- age 18 years or older
- indication to use an AFO during rehabilitation because of:
  - problems with stability in stance
  - problems with footclearance during swing
  - problems with foot prepositioning in early stance
- no severe deficits in communication
- no severe deficits in memory and understanding

### 4.3 Exclusion criteria

- medical history of previous stroke(s) without full physical recovery
- complicating medical history such as cardiac, pulmonary, or orthopaedic disorders that could affect performance of the included measurements
- severely impaired sensation
- suffering from severe neglect
- suffering from comprehensive aphasia
- participation in other scientific research

#### **4.4 Sample size calculation**

To our knowledge this is the first explorative research studying the effects of timing of AFOs in the rehabilitation after stroke. As such, data of earlier experiments with timing of AFOs are not available for power calculation.

The number of subjects that can be included in the study will depend on the number of acute stroke patients admitted to the rehabilitation centre. Based on estimations of therapists and rehabilitation physicians of the Roessingh Rehabilitation Centre and the Annual Reports of the Roessingh, we estimate that approximately 20 subjects can be included each year. The time during which subjects can be included is defined at 30 months (starting from September 2009). Within the available inclusion time of 30 months therefore 50 subjects can be included.

An interim power-analysis will be performed after including 30 subject to estimate whether including 50 subjects will be enough to reach sufficient statistical power. If this interim analysis reveals that more than the planned 50 subjects are needed, an amendment will be applied to include more subjects.

## 5. TREATMENT OF SUBJECTS

### 5.1 Investigational product/treatment

Acute stroke patients with indication for using an AFO will be included in this study. The intervention of interest is the timing of providing an AFO during the rehabilitation process. Early provision of AFOs (within one week after admission into the rehabilitation centre), will be compared with providing an AFO 8 weeks later.

There are several types of AFOs that are used in daily practice. Three commonly used types of AFOs are selected for this study (see pictures below). With the selected types of AFOs both patients with problems during the swing and stance phase of walking can be provided with an AFO. The so called “Dynafo” and “Ottobock” orthoses are flexible types of orthoses. They allow some dorsiflexion and vertical rotation movement in the ankle and are primarily used to correct a dropfoot and small varus deformities of the ankle and foot during the swing phase of walking. In case a higher degree of stability is needed, for example to counteract hyperextension of the knee in stance, or to correct varus deformity at the ankle in stance and/or swing due to spasticity, the “Camp” orthosis will be used. This is a more rigid type of AFO, which surrounds most of the calf and both malleoli, and therefore restricts most movement in the ankle. All AFOs are fixed with a band around the lower leg and are worn inside the shoe with a sole plate that extends below the foot. The selected AFOs can be provided for the left or right lower limb and are fabricated in various sizes. If necessary, for example in case of sensation disorders, the sole plate will be customized.

[figure not shown]

## 6. METHODS

### 6.1 Study parameters/endpoints

#### 6.1.1 Main study parameter/endpoint

In this study the effects of early provision of ankle-foot orthoses will primarily be assessed on the level of the ICF level “activities”. The included parameters (see below) will assess the effects on the patient’s mobility and daily life activities.

##### Mobility related activities and activities of daily living

On the ICF level “activities” the effect of timing of providing AFOs is assessed on mobility and activities of daily life. Therefore, several clinical tests are used: 10m walking test (Wade, 1992), 6min walking test, Functional Ambulation Categories (Holden et al. 1984), Timed Up&Go test (Podsiadlo and Richardson, 1991), Stairtest (de Wit et al. 2004), Rivermead Mobility Index (Collen et al. 1991), Berg Balance Scale (Berg et al. 1989), Barthel Index (Collin et al. 1988), Nottingham extended ADL - index (Harwood and Ebrahim, 2002).

Walking velocity:

- 10m walking test (10MWT): comfortable walking speed is measured over a distance of 10m. If necessary walking aids are allowed, physical help is not allowed. Walking speed is calculated by averaging the results of 3 performances.

Walking endurance:

- 6min walking test (6MWT): Comfortable walking speed is measured during 6 minutes. The distance covered in 6 minutes is measured. In case the subject stops before the 6 minutes are over, time and distance are reported.

Independence of walking:

- Functional Ambulation Categories (FAC): evaluates the degree of independence in walking. Performance is graded on a 6-point scale, with higher scores reflecting increasing independence of walking.

Mobility:

- Timed Up&Go test (TUG): The examiner times the subject as he/she performs the following activity: from a sitting position in a standard-height armchair, the subject independently stands up, walks 3 meters (with assistive device as needed), turns around, walks back and sits down again. The average of 3 tests is calculated.
- Stairtest (ST): assesses mobility like the TUG, with addition of 2 tasks: stairs ascent and descent. Patients are timed while rise from a chair, walk and ascend a flight of 12 stairs, walk and touch a

wall, turn around, descend the stairs, walk back to the chair and sit down again. The average time of 3 tests is calculated.

- Rivermead Mobility Index (RMI): a questionnaire with 15 items concerning mobility, graded on a 2-point scale.

Balance:

- Berg Balance Scale (BBS): evaluates balance and is composed of 14 balance tasks that require the subject to maintain a static position, change the orientation of the centre of mass with respect to the base of support and diminish the base of support. Performance of each task is graded from 0 (cannot perform) to 4 (normal performance).

Activities of daily life:

- Barthel Index (BI): evaluates the level of independence during activities of daily life. Ten items are evaluated on a 2/3/4-point scale.
- Nottingham Extended ADL – Index (NEADL): evaluates the level of independence during extended activities of daily life. Twenty-two items are evaluated on a 4-point scale.

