### **8.2 Univariate analysis**

A significance level of  $\alpha = 0.05$  will be used in data analysis. If necessary, adjustments for multiple comparisons will be applied.

Analysis of this study consists of studying the effects of timing of providing AFOs on the outcome measures. Comparison of the data between the “early” and “late” AFO group will be performed using corresponding parametric/non-parametric tests according to the features of the outcome measures involved (t-test).

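### Three timed main endpoints (10MWT, TUG, Stairtest) give no value for a subject who cannot perform them, so a comparison of the values they produce is made in groups that the treatment helps to select

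*Protocol*

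**What the plan says.** Section 6.1.1 lists nine measures as main endpoints. Four of them require walking.

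- **10 m walking test (10MWT).** "If necessary walking aids are allowed, physical help is not allowed". The result is a mean: "Walking speed is calculated by averaging the results of 3 performances".
- **Timed Up&Go (TUG).** It is timed while "the subject independently stands up, walks 3 meters (with assistive device as needed"; three tests are averaged.
- **Stairtest.** A timed course that includes 12 stairs: "The average time of 3 tests is calculated".
- **6-minute walking test (6MWT).** Comfortable speed and the distance covered are both mentioned. For early stoppers, "In case the subject stops before the 6 minutes are over, time and distance are reported".

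None of these entries says what is recorded for a subject who cannot do the test. The Berg Balance Scale, in the same section, does have a floor: "Performance of each task is graded from 0 (cannot perform) to 4 (normal performance".

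Section 4.2 admits subjects up to six weeks after stroke with an "indication to use an AFO during rehabilitation because of" stance, foot-clearance or foot-prepositioning problems. Neither 4.2 nor 4.3 sets a minimum walking ability. The hypothesis in section 2 expects early provision to improve walking independence as well as speed and endurance. Section 6.3 and Table 1 schedule the four tests every two weeks to week 18, then at T26 and T52. Section 8.2 plans "corresponding parametric/non-parametric tests according to the features of the outcome measures involved (t-test" being the only test named).

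**The concern.** A mean of three performances does not exist for someone with no performance. As 6.1.1 is written, such a subject has no 10MWT speed, TUG time or Stairtest time at that visit and contributes nothing to the comparison.

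This would matter less if inability were unrelated to allocation, but the protocol's own hypothesis says otherwise: early AFO should make more people independent walkers. If so, the early group's mean takes in people who have only just become able to walk, while their counterparts in the late group are absent from the late mean. The two sets of performers are then not comparable by randomisation. The distortion runs against the trial's hypothesis, because the people added to the early group are likely to be slow.

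The mechanism is strongest up to T9, when only the early group has an AFO. Section 3 itself foresees that some late-group subjects will find it impossible to practise without ankle support.

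**Working it through.** **Inputs from the protocol.** 20 subjects per year for 30 months: 20 × 30/12 = 50, which reproduces the planned number in 4.4. With two groups and blocks of four I take 25 per arm (equal allocation is not stated outright). α = 0.05, taken as two-sided. The protocol gives no effect size, SD, walking speed or inability rate, so everything below on size is an assumption shown over a range. Section 1 cites 60% functional independence six months after stroke, but for a broader population and a broader notion of independence. It is not an inability rate for these tests.

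**Model A: common shift.** Walking ability is normal with SD 1, and a test is scored only above a threshold placed at 0. If a share p of the late group is unable, the late mean is μ = −Φ⁻¹(p) and the early mean is μ + d. The mean among performers is m(μ) = μ + φ(μ)/Φ(μ).

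- p = 0.30, d = 0.5. Late: μ = 0.524, m = 0.524 + 0.348/0.700 = 1.021. Early: 1.024 + 0.236/0.847 = 1.303. Difference among performers: 1.303 − 1.021 = **0.282 SD**.
- p = 0.40, d = 0.5. Late: 0.253 + 0.386/0.600 = 0.897. Early: 0.753 + 0.300/0.774 = 1.141. Difference: **0.244 SD**.

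Share of the true shift still visible among performers, for d from 0.3 to 0.8:

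| Late group unable | Share retained |
|---|---|
| 10% | 75-81% |
| 30% | 53-61% |
| 40% | 46-53% |
| 50% | 40-46% |

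The benchmark matters. If all subjects are compared with the unable scored 0, the difference is Φ(μ+d)·m(μ+d) − Φ(μ)·m(μ). For p = 0.30 and d = 0.5 this is 0.847 × 1.303 − 0.700 × 1.021 = 0.389, so the performers' difference is 0.282/0.389 = 72% of it. Over 10-60% unable, this ratio is 70-86%. Model A never changes the sign.

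**Model B: new walkers.** Let p₀ and p₁ be the shares unable in the late and early groups. Subjects able in either group walk at 0.50 m/s and gain g from early AFO; subjects made able by early AFO walk at 0.20 m/s.

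- p₀ = 0.40, p₁ = 0.20, g = 0. Early performers: (0.60 × 0.50 + 0.20 × 0.20)/0.80 = 0.425 m/s against 0.50, a difference of −0.075. All subjects with zeros: 0.34 − 0.30 = +0.04.
- Same shares, g = 0.05. Performers −0.038; all subjects +0.07.
- Break-even gain: g = (p₀ − p₁)(0.50 − 0.20)/(1 − p₀). This is 0.2 × 0.3/0.6 = 0.10 m/s for 40% against 20% unable, and 0.1 × 0.3/0.7 = 0.043 m/s for 30% against 20%. Below it the sign among performers is reversed.

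**Power.** Under Model A with d = 0.8, 25 per arm and 4,000 simulated trials per row:

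| Late group unable | t-test, performers only | Rank test, all subjects, unable ranked worst |
|---|---|---|
| 30% | 46% | 76% |
| 40% | 37% | 75% |
| 50% | 28% | 73% |

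A t-test on the unobservable latent ability would have about 80%. Performers-only power falls both because the difference shrinks and because subjects are lost.

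**The case against.** The protocol nowhere says that non-performers are dropped. Section 8.2 already allows non-parametric tests, section 6.3 refers test conduct to the specific test protocols, and an SAP that is not shown could assign a zero or worst rank. A reader might infer that a performers-only t-test is planned; the text does not support that. What stands is that the derivations in 6.1.1 produce no value that would keep these subjects in, and a rank test does not help unless inability has a rank. Recording is also a matter for the protocol: if inability is left blank on the form, it may not be separable later from a missed visit. Assessors are not blinded (6.2), so the rule is better fixed beforehand.

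Three further readings go too far. Needing a cane does not leave a subject unscored: aids are allowed, and on the 10MWT the bar is physical help. On the 6MWT one might fear that distance is divided by time walked, so that stopping early goes unnoticed; section 6.1.1 says that distance is measured, and early stoppers have a recorded result. And it is not established that the effect will be halved or reversed. Halving is relative to a latent shift and needs about 40% or more unable; reversal needs a particular pattern of benefit, while section 2 expects speed to improve too.

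It is also fair that inability is partly captured elsewhere. The Functional Ambulation Categories are collected at the same visits, and the Berg, Rivermead, Barthel and Nottingham scales do not depend on a timed walk. That limits the damage to the trial as a whole but does not repair the timed endpoints. After T9 both groups have an AFO, so by T26 and T52 the bias may be small.

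**Conclusion.** The point holds in a limited form. 10MWT, TUG and Stairtest are undefined for subjects who cannot perform them, and the 6MWT is undefined for those who cannot start. Eligibility admits such subjects, and the hypothesis makes ability to perform an expected effect of treatment. Used as defined, these endpoints compare groups selected after randomisation, chiefly up to T9.

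The size cannot be derived from the documents. Under a normal common-shift model with 30-40% of the late group unable, 0.5 SD appears as 0.28-0.24 SD; with 10% unable, at least three quarters of the shift remains. Reversal is possible only where early AFO mainly produces slow new walkers and the gain in existing walkers is small: under 0.10 m/s or 0.043 m/s in the two cases worked above. The gap should be closed, and closing it is cheap.

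**What to change.** In section 6.1.1:

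- Record *unable* as a test result, distinct from a missed visit.
- Score it 0 m/s on the 10MWT, 0 m on the 6MWT, and worst rank on TUG and Stairtest.
- State that the 6MWT endpoint is total distance in six minutes, with early stoppers keeping the distance reached.

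In section 8.2:

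- Compare these four endpoints by a rank test over all randomised subjects assessed at the visit.
- Report the proportion able to perform each test, by arm and visit.

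The cost is a few sentences and one extra code on the case report form; visits, tests and treatment are unchanged. The drawback is that the result then combines ability with speed, and zero or worst rank is a choice of estimand. Performers-only mean speeds and times can still be shown as a secondary description, labelled as not being a randomised comparison.

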### 6.1.2 Secondary study parameters/endpoints

When the effects of early provision of AFOs only measured only on the activity level, one cannot differentiate whether changes appear because of restoration of the paretic side or because of compensation by the non-paretic side. Therefore, secondly the effects of early AFO provision will be assessed of the ICF level “body function”. During gait analysis (see below) both the paretic and non-paretic side will be measured in order to explain changes on the activity level.

#### Walking impairment

Walking impairment (ICF level: body function) will be assessed during gait analysis measuring kinetics (ground reaction forces), 3D kinematics (joint angles) and temporal and spatial parameters of the walking pattern (step length, step time, step width, single/double stance time). Simultaneously, muscle activity from m. Rectus femoris, m. Vastus lateralis, m. Semitendinosus, m. Gastrocnemius and m. Tibialis anterior of both legs will be recorded using surface electromyography (EMG). Subjects will be measured while walking at comfortable speed, with and without AFO. If necessary, subjects are allowed to use walking aids like a cane.

Besides using gait analysis, body functions will be assessed using an instrumented test (Mappam procedure (Fleuren et al. 2006)) and clinical tests: the Motricity Index (Collin and Wade, 1990), Modified Ashworth Scale (Bohannon and Smith, 1987), Brunnstrom Fugl Meyer (leg portion, Fugl-Meyer et al. 1975), passive ankle angles (Ryf and Weymann, 1999).

- Mappam procedure: instrumented test to measure stretch reflex activity of the knee flexor and extensor muscles with surface EMG during the pendulum test (passive swing movement of the lower leg due to gravity) and during passive and active movement of the lower leg. Furthermore, the Visual Analog Scale (VAS-scale) will be used to assess the perception of spasticity and spasticity-related discomfort.
- Motricity Index (MI, leg portion): evaluates selective muscle control and maximal isometric muscle contraction of the lower limb, graded on a 6-point scale.
- Modified Ashworth Scale (MAS): evaluates the resistance to passive plantar and dorsal flexion in the ankle, graded on a graded on a 6-point scale.
- Brunnstrom Fugl Meyer assessment (BFM, leg portion): evaluates the amount of synergies in the lower limb, graded on a 3-point scale.
- Ankle angles (dorsiflexion, plantarflexion) during passive movement.

As secondary parameters fear of falling (Falls Efficacy Scale (Hellstrom and Lindmark, 1999), occurrence of falls and quality of life after stroke (Stroke Impact Scale, van der Port et al. 2008) are measured.

Falling:

- Falls Efficacy Scale (FES): evaluates the experienced confidence of the subject, and thereby the fear to fall, during activities of daily life, like walking outdoors or walking the stairs. Thirteen items are scored on a 11-point scale.

The occurrence of falls and all fall related events are measured using questionnaires for therapists and subjects (see attachment 1).

Quality of life:

- Stroke Impact Scale (SIS version 3.0): evaluates the effects of stroke in terms of function, activities and participation. Fifty-nine items are scored on a 5-point scale

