Besides measuring potential beneficial effects, possible adverse effects and the patients' opinion are important aspects that should be studied when evaluating the effects of using AFOs. In traditional neurodevelopment concepts of stroke physiotherapy AFO use is discouraged as AFOs are suggested to prevent or delay recovery of normal movement (Bobath, 1990). Immobilisation of the ankle may weaken the present muscles around the ankle, thereby inducing disuse and worsening the effect of loss of muscle strength. However, in a study by Geboers et al. immediate and long-term effects of AFOs on muscle activity during walking were studied in subjects with foot drop (Geboers et al. 2002). They concluded that AFO use by these recently paretic patients (peripheral paresis, 6 weeks to 1 year) did not seem to induce significant changes in muscle reaction after 6 weeks of daily use, compared with the immediate reaction. Therefore, they stated that no contraindications exist for AFO use in recent paretic subjects to enhance safe walking. Whether these effects also account for paresis after stroke is not clear. In addition to the discussion about the possible delaying effects of AFOs on recovery of normal movement, Tyson et al. studied the patients' opinion of using walking aids in non-ambulant acute stroke patients (Tyson and Rogerson, 2009). In a randomised controlled trial no assistive device, a walking cane, an AFO, a slider shoe, and walking with each of the devices was compared. When asked, 70% of the subjects would rather walk now using an assistive device than delay walking and learn to walk with a normative gait pattern without a device.

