### Clinical tests

All clinical tests and questionnaires measuring walking impairments, mobility, activities of daily life, falling and quality of life are performed according to the specific test protocols. During the first 18 weeks of the study most clinical tests will be repeated with 2-week intervals. Furthermore, the tests will be repeated 6 and 12 months after stroke (T26 and T52, respectively). All the clinical tests are performed with AFO.

The frequency of performing the various measurements is listed in Table 1.

Spasticity of the lower limb is assessed using the Mappam procedure. The subject is in a comfortable semi-reclined position (45°) with support for the back and lumbar region. Knee flexor and extensor muscles are recorded while performing the pendulum test (passive swing movement of the lower leg from full extension and then released), and during passive movement. The subject is instructed to relax his/her leg and not to oppose or facilitate the passive movements. The subject is asked to perform an active movement. The knee joint angle is measured with an electric goniometer placed on the lateral side of the knee. Surface EMG records the activity of the m. Rectus femoris and the Semitendinosus muscles. Electrode placement, skin preparation and related issues are performed according to the guidelines presented by SENIAM (Hermens et al. 1999).

Table 1: Measurements to be performed

| Period                               | Measurement                                                                                                                                                                                                                                                    | Content                                                                                                                                                                                |                                               |
|--------------------------------------|----------------------------------------------------------------------------------------------------------------------------------------------------------------------------------------------------------------------------------------------------------------|----------------------------------------------------------------------------------------------------------------------------------------------------------------------------------------|-----------------------------------------------|

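### The rule that all clinical tests are done with the AFO on reaches the ankle impairment tests: Ashworth and passive ankle angles would be taken through the orthosis, and before T9 in one arm only

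*Protocol*

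**What the plan says.** Protocol section 6.1.2 (Walking impairment) assesses body function by gait analysis, by one instrumented test (the Mappam procedure) and by a list introduced as "and clinical tests: the Motricity Index", followed by the Modified Ashworth Scale, the Fugl-Meyer leg portion and passive ankle angles. It describes them as follows:

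- Modified Ashworth Scale: "evaluates the resistance to passive plantar and dorsal flexion in the ankle".
- Passive ankle range: "Ankle angles (dorsiflexion, plantarflexion) during passive movement".
- Motricity Index: "evaluates selective muscle control and maximal isometric muscle contraction of the lower limb".
- Fugl-Meyer leg portion: synergies of the lower limb.

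Section 6.3 (Clinical tests) opens with the clinical tests and questionnaires, expressly including those for walking impairments, and says that they "are performed according to the specific test protocols". The same paragraph ends: "All the clinical tests are performed with AFO". No test, arm or visit is excepted.

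Section 5.1 says that the rigid Camp orthosis encloses most of the calf and both malleoli and "therefore restricts most movement in the ankle". The two flexible types allow some dorsiflexion.

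Sections 3 and 6.3 (Gait analysis) give the early group its AFO at the start of the T1 week and the late group its AFO in the T9 week.

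**The concern.** The AFO-on sentence makes sense for walking, stairs and balance, where performance with the device is the question. It does not suit tests whose object is the ankle itself. Resistance to passive ankle movement and passive ankle range, taken inside an orthosis that limits that movement, depend on the type and stiffness of the orthosis as well as on the patient.

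There is also a between-arm problem. Only the early arm has an AFO before T9, so a literal reading sets AFO-on against AFO-off in the randomised comparison, starting with the first measurement.

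These measures bear on a harm that the protocol raises itself. Section 1 (New research) reports the worry that "Immobilisation of the ankle may weaken the present muscles around the ankle", and section 9.3 lists interference with the recovery of normal movement as a risk. If early bracing reduced ankle range or changed tone, testing through the brace could hide it, and a brace effect could be read as stiffness or spasticity. Values collected under the wrong condition cannot be recovered in the analysis.

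**Working it through.** No sample size, power or alpha figure is involved. The check compares the texts and counts visits.

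**1. Does the rule reach these tests?** Section 6.1.2 calls all four clinical tests and places them under walking impairment. The section 6.3 paragraph names walking-impairment tests in its first sentence and puts all clinical tests under the AFO-on rule in its last. So the rule literally covers them. For gait analysis, by contrast, section 6.3 sets out when measurements are made with and without AFO. No such scheme exists for the clinical tests.

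**2. What does the device do to each test?**

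| Test | Object, per section 6.1.2 | Effect of testing through an AFO |
|---|---|---|
| Modified Ashworth Scale | passive resistance at the ankle | measurement defeated in Camp wearers, distorted in flexible-AFO wearers |
| Passive ankle angles | passive range at the ankle | as above |
| Motricity Index, leg | whole lower limb | any ankle component only; size unknown |
| Fugl-Meyer, leg | whole lower limb | any ankle component only; size unknown |

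Section 5.1 assigns the Camp type where more stability is needed, for example for varus due to spasticity. The distortion would therefore tend to be largest in patients whose spasticity the Ashworth is meant to grade.

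**3. At which visits does each arm have an AFO?** The inputs are Table 1 and the provision times above. Two assumptions are needed: the two-week grid starts at T1, and early-arm tests in the T1 week come after the AFO is provided.

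- Ashworth, Fugl-Meyer and ankle angles: T1, T9, T17, T26, T52 = 5 visits.
- Motricity Index: T1, T3, T5, T7, T9, T11, T13, T15, T17 = 9, plus T26 and T52 = 11 visits.

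The late arm is fitted in the T9 week, so its status at T9 depends on whether fitting or testing comes first.

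| | Visits | Early arm with AFO | Late arm with AFO | Arms differ |
|---|---|---|---|---|
| Ashworth, Fugl-Meyer, ankle angles | 5 | 5 | 3 to 4 | 5 − 4 = 1 to 5 − 3 = 2 |
| Motricity Index | 11 | 11 | 6 to 7 | 11 − 7 = 4 to 11 − 6 = 5 |

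The visits that certainly differ are T1 for the first three tests and T1, T3, T5 and T7 for the Motricity Index.

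**4. What follows for the comparison?** At the differing visits the between-arm contrast mixes device and impairment. T1 is the first measurement, so even the starting values are not comparable. At later visits the condition is the same in both arms, but both are tested through the device, and a true difference in ankle range or tone can be masked.

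**The case against.** The strongest reply is that section 6.3 also sends every clinical test, including the impairment tests, to its own test protocol, and section 6.1.2 gives a source for nearly all of them. An assessor who follows those may never test an ankle through an orthosis. The AFO sentence also cannot be carried out in the late arm before T9, which suggests that it was not drafted as an exhaustive rule. This part stands: the text is an unresolved conflict, not a deliberate instruction to measure the orthosis. It does not remove the problem, because the two sentences sit in one paragraph with no order of precedence. Section 6.2 says that assessors cannot be blinded, so the choice could vary by assessor or by arm.

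Several stronger readings are tempting, and the documents do not support them:

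- **That the ankle is tested through the device at every visit in both arms.** The late arm has no AFO before T9.
- **That all four tests become invalid.** The Motricity Index and the Fugl-Meyer are described as lower-limb tests and their items are not listed. The flexible orthoses allow some movement, and the rigid one restricts most movement, not all.
- **That the rule plainly covers Mappam.** Section 6.1.2 sets it apart as an instrumented test, and it concerns the knee. It is described under the Clinical tests heading in section 6.3, so a clarification is useful, but no error is shown.
- **That the check on restoration and on muscle disuse is lost.** Section 6.1.2 names gait analysis as the means of explaining changes at activity level. Gait analysis has its own with/without scheme and records EMG from tibialis anterior and gastrocnemius.

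**Conclusion.** The AFO-on sentence in section 6.3 is wrong as written for the ankle impairment tests. It defeats or distorts two of them, the Modified Ashworth Scale and passive ankle angles, and affects any ankle component of the Motricity Index and the Fugl-Meyer leg portion to a lesser degree that the documents do not let one quantify. It gives the arms different measuring conditions at 1 to 2 of 5 visits for three tests and at 4 to 5 of 11 for the Motricity Index, and it can mask a difference afterwards. It also conflicts with the reference to specific test protocols in the same paragraph.

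This rests on reading the sentence literally and on the two timing assumptions stated with the visit count. Only secondary endpoints of a self-described explorative study are affected. It should be fixed, but it does not threaten the main study parameters.

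**What to change.** In section 6.3 (Clinical tests):

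1. Limit the AFO-on sentence to the activity-level performance tests: walking, stairs, Timed Up and Go, and balance.
2. State that the Modified Ashworth Scale, passive ankle angles, the Motricity Index and the Fugl-Meyer leg portion are performed without AFO, in both groups, at every visit. Before T9 this is the only condition available in both arms, so it is the only one that keeps the comparison like with like throughout.
3. State the same condition for the Mappam procedure, for clarity.

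This also settles the conflict with the reference to specific test protocols. The cost is one or two sentences and the moment needed to take the AFO off. No visit, test or staff is added. If data have already been collected, record the AFO condition used at each of these tests, so that the affected values can be identified.
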